**Figure 2: Study Schematic (Cohort A1, Fasted versus Fed [High-fat Breakfast] and Additional Optional Cohorts A2 and A3)**

[figure not shown]

A = KL1333 administration; O = outpatient visit; PK = pharmacokinetics.

In Treatment Period 1, dosing will occur after an overnight fast of at least 8 hours. In Treatment Period 2, dosing will occur 30 minutes after starting a high-fat breakfast. The washout will be at least 10 days between doses (from Period 1, Day 1 to Period 2, Day 1).

[figure not shown]

A = KL1333 administration; PK = pharmacokinetics.

If additional cohorts are required, dietary state will be decided following review of data in Part A and available data from Part B.

The total duration of study participation for each subject (from Screening through Follow-up visit) is anticipated to be approximately 6 weeks for Cohort A1 and approximately 5 weeks for additional optional Cohorts A2 and A3.

### 3.1.2. Part B

Part B will comprise a randomised, multiple-dose, sequential-group, placebo-controlled study. Sixteen healthy subjects will be studied in 2 cohorts (Groups B1 and B2), with each cohort consisting of 8 subjects. Part B may start after completion of Group A1, at a dose equal to or less than given in Part A.

Potential subjects will be screened to assess their eligibility to enter the study within 28 days prior to the first dose administration. All subjects will participate in 1 treatment period and will reside at the Phase I clinical site from Days -1 to 12 (48 hours post final dose). Subjects will return to the clinical site for outpatient visits on Days 13 and 14.

On Day 1, 6 subjects will be randomised to receive KL1333 and 2 subjects will be randomised to receive placebo. The preliminary planned doses of KL1333 for Groups B1 and B2 are 25 and 50 mg, respectively, once daily (QD) on Days 1 to 10. Dose levels, dose frequency, and dietary state will be confirmed following review of safety, tolerability, and PK data from Part A and ongoing data from Part B. Additionally, a dose selection conference meeting will be held before each cohort in Part B where blinded data from the previous cohort will be reviewed before a decision is made about proceeding to the next cohort. Following review of safety, tolerability, and PK data, up to 3 additional dose cohorts of

healthy subjects may be added to further explore the PK, safety, and tolerability of KL1333. If additional cohorts are required, each cohort will consist of 8 subjects, with 6 subjects receiving KL1333 and 2 subjects receiving placebo. The dose level will not exceed 600 mg, and the predicted exposure following multiple daily dose administration in any subject in Part B will not exceed an  $AUC_{0-24}$  of 51,800 ng.h/mL for derived total KL1333. There will be a minimum of 6 days between dose escalations for each cohort (between the last dose of one cohort and the first dose of the next cohort).

Subjects will return for a Follow-up visit on Day 15, 5 days after their final dose.

An overview of the study design is shown in [Figure 3](#).

**Figure 3: Study Schematic (Part B)**

[figure not shown]

▲ = biomarker sample; PK = pharmacokinetics.

Dietary state will be confirmed from review of data from Part A and available data from Part B.

The total duration of study participation for each subject (from Screening through Follow-up visit) is anticipated to be approximately 6 weeks for Part B.

### 3.1.3. Part C

Part C will comprise a randomised, multiple-dose, single-group, placebo-controlled study. A total of 8 patients diagnosed with any mitochondrial disease will be enrolled in this part of the study. Part C may start after the dose selection conference has been completed for the final cohort of Part B, at a daily dose no higher than the highest well-tolerated dose in Part B.

Potential study patients will be screened to assess their eligibility to enter the study within 75 days prior to the first dose administration. Patients will reside at the clinical site, or nearby the clinical site at a hotel recommended by the clinical site, from Days -1 to 2 and Days 10 to 11. Patients will return to the clinical site for outpatient visits on Days 4 and 8. Patients will be randomised on Day 1.

Two patients will be dosed initially, with 1 patient receiving KL1333 and 1 patient receiving placebo. If there are no safety or tolerability concerns in these patients following the Day 4 visit, the remaining 6 patients, with 5 patients receiving KL1333 and 1 patient receiving placebo, will be enrolled on a rolling basis. In the event there are safety concerns following completion of the 2 sentinel patients without meeting stopping criteria, the Sponsor may add intermediate cohorts. The dosing schedule of intermediate cohorts will be the same as that of the planned cohort. The schedule of safety assessments of intermediate cohorts will be the same as that of the planned cohort as a general rule. Whether or not to add safety assessments in the intermediate cohorts will be determined by the Sponsor.

It is planned for patients to receive study drug QD on Days 1 to 10. Dose levels, dose frequency, and dietary state will be confirmed following review of safety, tolerability, and PK data from Part B, and unless deemed very unfavourable for the conduct of the study, the patients will not be required to be fasting prior to dosing. Study drug will be administered by clinical site staff when the patients are resident at the clinical site or return for outpatient visits. On all other days, patients will record drug administration and any concomitant medications in a diary that will be provided to each patient. Diaries will be reviewed and checked for compliance during the outpatient visits and as part of the check-in procedures on Day 10. Clinical symptoms that occur while patients are not resident at the site will be collected by the site using standard AE reporting procedures.

Patients will return for a Follow-up visit on Day 15, 5 days after their final dose.

An overview of the study design is shown in [Figure 4](#).

**Figure 4: Study Schematic (Part C)**

[figure not shown]

Dietary state will be confirmed from review of data from Part B and unless deemed very unfavourable for the conduct of the study, the patients will not be required to be fasting prior to dosing.

a Patients can reside at the clinical site or nearby the clinical site at a hotel.

The total duration of study participation for each patient (from Screening through Follow-up visit) is anticipated to be approximately 7-11 weeks for Part C.

### 3.1.4. Part D

Part D will comprise a randomised, multiple-dose, placebo-controlled study. Sixteen healthy subjects will be studied in 2 cohorts (Groups D1 and D2), with each cohort consisting of 8 subjects. Part D will start after completion of Part B, and the Part D groups may be run in parallel.

Potential subjects will be screened to assess their eligibility to enter the study within 35 days prior to the first dose administration. All subjects will participate in 1 treatment period and will reside at the Phase I clinical site from Days -1 to 12 (48 hours post final dose). Subjects will return to the clinical site for outpatient visits on Days 13 and 14.

On Day 1, 6 subjects will be randomised to receive KL1333 and 2 subjects will be randomised to receive placebo in each group. The doses of KL1333 for Groups D1 and D2 are 75 mg twice daily (BID) and 50 mg 3 times daily (TID), respectively, on Days 1 to 10 with a single dose administration on Day 10. The first dose on Day 1 and the dose on Day 10 will be administered following an overnight fast of at least 8 hours due to intensive PK sampling. The first dose on Day 7 will be administered following an overnight fast of at least 8 hours due to clinical laboratory evaluations.

Subjects will return for a Follow-up visit on Day 15, 5 days after their final dose.

An overview of the study design is shown in [Figure 5](#).

**Figure 5: Study Schematic (Part D)**

[figure not shown]

▲ = biomarker sample; PK = pharmacokinetics.

Dosing will be twice daily for Group D1 and 3 times daily for Group D2. There will be a single dose administration on Day 10.

Subjects will be fasted for the first dose on Day 1 and single dose on Day 10 for intensive pharmacokinetic sampling and the first dose on Day 7 for clinical laboratory evaluations. All other doses may be given without regard to food.

The total duration of study participation for each subject (from Screening through Follow-up visit) is anticipated to be approximately 7 weeks for Part D.

Schedules of Assessments are presented in [Appendix 5](#).

### 3.2. Study Start and End of Study Definitions

The start of the study is defined as the date the first subsequently enrolled subject signs an Informed Consent Form (ICF). The point of enrolment occurs at the time of subject number allocation. The end of the study is defined as the date of the last subject's last study-specific assessment visit (scheduled or unscheduled).

### **3.3. Additional Groups**

Following review of the safety, tolerability, and PK data, additional dose cohorts (not to exceed the exposure limits in [Section 3.7](#)) may be added to the study. Up to 2 further cohorts of 8 subjects (6 active:2 placebo) may be included in Part A and up to 3 further cohorts of 8 subjects (6 active:2 placebo) may be included in Part B. The requirement for additional cohorts will be agreed with the Sponsor.

### **3.4. Discussion of Study Design, Including the Choice of Control Groups**

As KL1333 has previously been given as single ascending doses to Korean subjects in Study KL1333\_101, Part A is planned to have 1 single-dose cohort to compare single-dose PK data in non-Korean subjects before administering multiple doses to non-Korean subjects. A crossover design has been chosen to study the food effect, as this gives a within-subject assessment of the influence of food on the PK of KL1333 and so increases the power of the study for the given number of subjects. For Part B, a sequential-group, ascending-dose design has been chosen for safety reasons as KL1333 is in the early stages of clinical development, and this will be the first time it will be administered in multiple doses to humans. Oral doses have been chosen for this study, as this is the intended clinical route of administration and based on the results of the single ascending dose study.

It is the intent of Part B to dose subjects such that steady-state plasma levels of KL1333 are achieved and maintained for several days. Based on the available single ascending dose data, it is expected that this will be achieved following 10 days of once-daily dosing; additionally, a full review of all the safety, tolerability, and PK data from Part A will be performed to confirm the dose regimen for Part B.

Based upon the nonclinical data and the data from the single ascending dose study, the duration of each treatment period is considered adequate to achieve the study objectives. An interval of at least 10 days between treatment periods in Part A is considered adequate to prevent carryover of KL1333, given the observed mean half-life for free KL1333 of 13.73 to 34.64 hours in the single ascending dose study.

This study will be double-blind and placebo-controlled in order to avoid bias in the collection and evaluation of data during its conduct. Placebo has been chosen as the control treatment to assess whether any observed effects are treatment related or simply reflect the study conditions. The safety and PK assessments are standard parameters for clinical studies in drug development. Based on the PK data from Study KL1333\_101, the plasma sampling timepoints are expected to sufficiently estimate PK parameters of KL1333 exposure.

Conducting Parts A, B, and D in healthy subjects mitigates the potential confounding effects of the disease state and concomitant medications. Conducting Part C in patients with mitochondrial disease allows for a preliminary assessment of KL1333 in patients, including a preliminary exploration of the selected clinical assessments ([Section 7.2.3](#)).

Blood samples will be taken to assess the effect of multiple doses of KL1333 on the selected biomarkers. Blood samples will also be taken for possible later analysis of metabolomics. Continuous 12-lead ECG monitoring will be included in the healthy subjects in this study to collect data that will allow for future investigation of potential KL1333 effects on the QT

interval, with a view of supporting a potential thorough QT study waiver. Blood samples will be taken in case unexpected variability is seen in the PK data that would warrant NQO1 genotyping as there is a variant allele of this enzyme that is associated with a reduction in NQO1 protein and activity that has been shown to be more common in the Korean population than the non-Hispanic white population.

As a result of gastrointestinal AEs seen to date in this study, supplementary safety assessments for C-reactive protein (CRP), erythrocyte sedimentation rate (ESR), and faecal calprotectin will be assessed in Group B5 and Part D healthy subjects and if required/indicated in Part C patients to better evaluate the gastrointestinal AEs by exploring potential levels of general and gastrointestinal tract inflammation.

Part D was added to this study to investigate if splitting the KL1333 dose throughout the day will improve safety and tolerability and increase exposure. This part will include one 75 mg KL1333 BID cohort and one 50 mg KL1333 TID cohort to compare to the 150-mg QD cohort in Part B. To obtain further PD information in Part D, postdose blood samples for biomarkers and metabolomics will be collected and whole blood metabolomics will be evaluated in addition to the serum metabolomics that was performed in Parts A through C. The 2 dose cohorts in Part D may be run in parallel as Part B was completed prior to the addition of Part D to the protocol.

#### **3.4.1. Dose Interval**

As KL1333 has already been administered as single doses to Korean subjects up to 800 mg in Study KL1333\_101, all subjects in a given dose cohort in Parts A and B of this study can be dosed on the same day.

Dosing in Part C will be such that 2 patients (1 KL1333 and 1 placebo) will be dosed initially as an extra precaution given the fragile patient population. If there are no safety or tolerability concerns per the Investigator in these patients following the Day 4 visit, the remaining 6 patients, with 5 patients receiving KL1333 and 1 patient receiving placebo, will be enrolled on a rolling basis.

All subjects in a given dose cohort in Part D of this study can be dosed on the same day; doses of up to 250 mg KL1333 QD in Part B were shown to be safe and moderately well tolerated (no dose escalation stopping criteria were met), although frequent gastrointestinal AEs were reported prior to the addition of Part D.

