### **3.6. Dose Escalation**

In Part B, doses will be administered in an escalating manner following satisfactory review by the Sponsor and Phase I healthy subject clinical site Investigator of the safety, tolerability, and PK data from the lower dose levels (including Part A). The review will include safety and tolerability data up to 48 hours postdose, as this covers approximately 2 times the anticipated  $t_{1/2}$  and most AEs in Study KL1333\_101 were reported within 48 hours postdose, and PK data up to 5 days postdose, as this is approximately 5 times the anticipated  $t_{1/2}$ . There

will be a minimum of 6 days between dose escalations (between the last dose of one cohort and the first dose of the next cohort) to allow sufficient time for analysis of KL1333 PK samples through 5 days postdose and an adequate safety review.

Doses may be reduced and may be lower than the planned doses.

Dose escalation in Part B will only occur if data from a minimum of 6 subjects have been reviewed from the previous lower dose cohort, such that data from a minimum of 4 subjects who have received KL1333 will be used to make the dose escalation decision.

The justification for this is as follows:

- Based upon nonclinical data, no clinically important off-target effects are expected within the proposed dose range.
- A minimum of 4 subjects receiving the active drug is considered sufficient to characterise the safety profile and PK response to KL1333.

Between each dose escalation, the Phase I healthy subject clinical site Investigator will review all available blinded data to ensure it is safe to proceed with the planned dose escalation. An interim safety report, summarising results from all available safety assessments, will be sent to the Sponsor prior to the start of each successive cohort. Any clinically significant results will be discussed with the Sponsor before dose escalation continues. Interim PK data will also be reviewed in terms of dose escalation and to confirm that the study design remains appropriate. In the event of a disagreement between the Sponsor and Phase I healthy subject clinical site Investigator on the dose escalation decision, the decision of the Investigator will be upheld.

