### **3.7. Dose Escalation Stopping Criteria**

The dose level for this study will not exceed 600 mg. In addition, dosing will be stopped and dose progression will be halted until safety information can be reviewed in the event that:

- One or more subjects experience a serious AE (SAE) that is considered to be related to IMP or 2 or more subjects experience severe AEs that are considered to be related to IMP
- There is evidence of clinically significant increases in liver function tests (aspartate aminotransferase, alanine aminotransferase, alkaline phosphatase, bilirubin, and/or gamma-glutamyl transferase), defined as 3 times the upper limit of normal in 3 or more subjects in a cohort compared to Day -1 measurements (confirmed with repeat testing)
- QTcF increases >60 msec compared to baseline and/or absolute QTcF values >500 msec (confirmed by single repeat measurement) in 2 or more subjects in a cohort

- Severe diarrhoea, defined as 7 or more episodes, rated as  $\geq 5$  on the Bristol Stool Chart, in 1 day for 2 consecutive days in 2 or more subjects in a cohort
- The exposure for any subject in the planned dosing cohort is predicted to exceed an  $AUC_{0-24}$  of 51,800 ng.h/mL for derived total KL1333 (as the sum of parent KL1333, de-conjugated glucuronidated KL1333 metabolites, and sulphated KL1333 metabolites). For Part D,  $AUC_{0-24}$  will be determined as  $AUC_{0-\tau} \times 2$  for BID and  $AUC_{0-\tau} \times 3$  for TID regimens.

If, following an internal safety review, the Sponsor deems it appropriate to restart the study, this can be done following approval of a substantial protocol amendment.

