### **5.3. Randomisation**

The randomisation code will be produced by the statistics department at Covance using a computer-generated pseudo-random permutation procedure. In each part of the study, 2 subjects per dose cohort will be randomly assigned to receive placebo. Subjects in

Group A1 will receive the same treatment in Treatment Periods 1 and 2. For Part C, sentinel dosing will occur whereby 2 patients (1 active and 1 placebo) will be dosed on Day 1 and, providing no safety concerns arise following the Day 4 visit, the remaining 6 patients can be dosed.

Prior to the start of the study, a copy of the master randomisation code will be supplied in sealed envelopes to the sites' pharmacy staff and the biopharmaceutical analyst at the bioanalytical laboratory.

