### **7.3.2. Clinical Laboratory Evaluations**

Blood and urine samples will be collected for clinical laboratory evaluations (including clinical chemistry, haematology, urinalysis, and serology) at the times indicated in the Schedule of Assessments in [Appendix 5](#). Clinical laboratory evaluations are listed in [Appendix 2](#). Additional clinical laboratory evaluations will be performed at other times if judged to be clinically appropriate or if the ongoing review of the data suggests a more detailed assessment of clinical laboratory safety evaluations is required.

All subjects will be asked to provide urine samples for drugs of abuse screen and will undergo an alcohol breath test at the times indicated in the Schedule of Assessments in [Appendix 5](#). Subjects in Parts A, B, and D will also provide urine samples for cotinine testing at the times indicated in the Schedule of Assessments in [Appendix 5](#). Subjects in Part C will have glycated haemoglobin measured at Screening. For all female subjects, a pregnancy test will be performed at the times indicated in the Schedule of Assessments in [Appendix 5](#). For all postmenopausal female subjects, follicle-stimulating hormone will be assessed at Screening.

An Investigator (or designee) will perform a clinical assessment of all clinical laboratory data.

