| Clinical laboratory evaluations g                                             | X                             | X         | Day 7: Predose
Day 10: Predose and 48 hours postdose                                                                                                                                                                                            |                          | X                    | X                     |
| C-reactive protein, erythrocyte sedimentation rate, and faecal calprotectin h |                               | X         | Days 4 and 10: Predose                                                                                                                                                                                                                             |                          |                      | X                     |
| Blood pressure, pulse rate, and body temperature i                            | X                             | X         | Day 1: Predose and 2, 4, and 12 hours postdose
Days 2 to 10: Predose
Days 11 and 12                                                                                                                                                          | X                        | X                    | X                     |

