**Table 3: Schedule of Assessments – Part C**

| Study Procedures                                                                         | Screening
(Days -75
to -2) | Day
-1 | Day
1                                | Day
2       | Day
3 | Day
4       | Days
5 to
7 | Day
8       | Day
9 | Day
10      | Day
11 | ET | Follow-up
(Day 15) |
|------------------------------------------------------------------------------------------|----------------------------------|-----------|-----------------------------------------|----------------|----------|----------------|-------------------|----------------|----------|----------------|-----------|----|-----------------------|
| 30 Second Sit-to-Stand Test                                                              |                                  | X         |                                         |                |          |                |                   |                |          | X              |           | X  |                       |
| Safety and tolerability:                                                          |                                  |           |                                         |                |          |                |                   |                |          |                |           |    |                       |
| Adverse event recording                                                                  | X                                | X         | X                                       | X              | X        | X              | X                 | X              | X        | X              | X         | X  | X                     |
| Prior/concomitant medication monitoring                                                  | X                                | X         | X                                       | X              | X        | X              | X                 | X              | X        | X              | X         | X  | X                     |
| Clinical laboratory evaluations j                                             | X                                | X         |                                         |                |          |                |                   | X g |          | X g | X         | X  | X                     |

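### Part C releases the remaining six patients after the sentinels' Day 4 visit, but the first scheduled on-treatment safety laboratory sample is predose on Day 8

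*Protocol*

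**What the plan says.** The release rule appears in four places, all tied to Day 4. Section 3.4.1 has "If there are no safety or tolerability concerns per the Investigator in these patients following the Day 4 visit". Section 3.1.3 has "If there are no safety or tolerability concerns in these patients following the Day 4 visit, the remaining 6 patients", and the Part C synopsis says the same. Section 5.3 has "providing no safety concerns arise following the Day 4 visit, the remaining 6 patients can be dosed". The six comprise five on KL1333 and one on placebo, enrolled on a rolling basis. Section 3.4.1 justifies the sentinel pair as added caution because these patients are frail.

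In Appendix 5, Table 3, the row "Clinical laboratory evaluations j" is marked at Screening, Day -1, Day 8 (predose), Day 10 (predose), Day 11, early termination and Follow-up. The columns for Days 1, 2, 3, 4 and 5 to 7 are empty. The footnote defines the row as chemistry, haematology and urinalysis. The optional inflammation markers (CRP, ESR, faecal calprotectin) are marked only on Day -1 and predose on Day 10.

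Section 7.3.2 allows unscheduled tests: "Additional clinical laboratory evaluations will be performed at other times if judged to be clinically appropriate", or if ongoing data review calls for them.

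**The concern.** A sentinel step protects later patients only through what is known when they are released. Section 2.2.1 makes laboratory abnormalities a primary safety endpoint, yet nothing in the schedule gives the Investigator an on-treatment laboratory value from either sentinel by Day 4. Adverse events, vital signs, ECGs and a symptom-directed examination would not show an asymptomatic liver, renal, creatine kinase or haematology change.

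The population makes this more than a formality. Under Section 4.1, Part B subjects had to be free of clinically significant laboratory findings. Part C admits patients with creatinine clearance down to 45 mL/min (Section 4.2, criterion 34) and allows approved chronic medication (Section 6.1). Part B could not show how such patients respond; the sentinel step could.

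**Working it through.** The protocol gives no figure to reproduce here. The check sets the schedule against the release rule and counts doses.

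**1. Scheduled data available in Part C by the Day 4 visit (Appendix 5, Table 3)**

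| Assessment | On-treatment time points up to Day 4 |
|---|---|
| Adverse events | Days 1 to 4 |
| Vital signs | Day 1 (2, 4 and 10 h postdose), Day 2 predose, Day 4 predose |
| Triplicate ECG | Day 1 (2 h postdose), Day 2 predose, Day 4 predose |
| Symptom-directed examination | Day 2 predose, Day 4 predose |
| Chemistry, haematology, urinalysis | none |
| CRP, ESR, calprotectin (optional) | none |

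Lactate and pyruvate are drawn predose on Days 2 and 4 as pharmacodynamic biomarkers. No text makes those results part of the release decision, and they are not liver, renal or haematology tests.

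**2. Timing, assuming the planned once-daily dosing on Days 1 to 10**

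- Gap from the Day 4 visit to the first on-treatment laboratory draw: 8 − 4 = 4 days.
- Doses taken by the active sentinel before a predose Day 8 draw: Days 1 to 7 = 7.
- Doses taken before a predose Day 4 draw, if one were added: Days 1 to 3 = 3.

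**3. Exposure of later patients before the sentinel Day 8 draw**

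- Upper bound: all 5 active patients start on sentinel Day 5, so 5 × 3 (Days 5, 6, 7) = 15 active doses.
- Lower bound under rolling enrolment: 0.
- Laboratory turnaround after the Day 8 draw would add to this.

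**4. The liver stopping rule**

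Section 3.7 words it as "defined as 3 times the upper limit of normal in 3 or more subjects in a cohort compared to Day -1 measurements". The sentinel pair has 2 members, and 2 < 3, so the rule cannot be met by the sentinels alone.

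**5. What a Day 4 sample could detect**

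Let *p* be the assumed proportion of treated patients showing a laboratory change by Day 4. With one active sentinel, the probability that the sample shows it is *p*. The probability that at least one of the next five active patients would show it is 1 − (1 − *p*)^5, assuming independence.

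| Assumed *p* | Seen in the one active sentinel | At least one of the next five |
|---|---|---|
| 0.10 | 10% | 1 − 0.9^5 = 41% |
| 0.20 | 20% | 1 − 0.8^5 = 67% |
| 0.50 | 50% | 1 − 0.5^5 = 97% |

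The protocol does not give these rates; the range is illustrative.

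**6. Is Day 4 too early to be informative?**

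Section 3.6 treats 48 hours as about 2 half-lives, so the half-life is about 24 hours. Assuming linear kinetics, three daily doses bring exposure to about 1 − 0.5^3 = 87.5% of steady state by predose Day 4. Some laboratory changes may lag behind exposure.

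**7. Part B for comparison**

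Section 3.6 says of the review before the next cohort: "The review will include safety and tolerability data up to 48 hours postdose". Table 2 schedules laboratory samples predose on Day 7 and then "Day 10: Predose and 48 hours postdose", so on-treatment laboratory data inform that decision. It is a dose decision between cohorts, not a sentinel release. The comparison shows only that the protocol uses such data for release elsewhere.

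**The case against.** The strongest reply is that the protocol contradicts nothing. Release rests on the Investigator's judgement, no text promises that laboratory results will inform it, and the Day 4 assessments suit the known signal, which is gastrointestinal and symptomatic. Part B dosed whole cohorts with no sentinel and took its first on-treatment laboratory sample predose on Day 7, after 6 doses, so Part C is already the more cautious design.

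There are further safeguards:

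- Part B reached 250 mg once daily with no stopping criterion met, and the liver rule is one of those criteria. The Part C dose may not exceed the highest well-tolerated Part B dose.
- Patients must be clinically stable, judged partly on laboratory results at Screening and Check-in (Section 4.1, criterion 10). Chronic medication needs Medical Monitor and Investigator approval, and criteria 29 and 30 of Section 4.2 exclude interacting drugs.
- Section 7.3.2 also lets ongoing data review prompt extra tests, which does not depend on symptoms.
- Even in the 15-dose case, each later active patient has had at most 3 of 10 doses when the sentinel Day 8 sample is drawn. Withdrawal, study discontinuation and intermediate cohorts (Sections 4.4, 4.5 and 3.1.3) remain available.

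Much of this stands. It lowers the probability and consequence of a missed change, and it makes this a design weakness, not a misstatement. But no safeguard puts a laboratory value from the active sentinel before the Investigator at release. Discretionary tests may never be ordered for a silent change, and the later controls cannot act on a value not yet measured. It is also true that one active patient after 3 doses, reviewed blind beside one on placebo, gives limited detection. That limits the benefit of the remedy, whose cost is also small.

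**Conclusion.** The concern holds. As scheduled, the decision to expose five more patients to KL1333 is made with zero on-treatment safety laboratory samples. The first comes 4 days after the Day 4 visit, after 7 doses in the active sentinel, with between 0 and 15 active doses possibly given to later patients by then. The 15 assumes once-daily dosing and all five starting the day after the visit, which rolling enrolment makes unlikely. The detection probabilities rest on assumed event rates. The protocol should be changed on this point, but the existing safeguards mean that the gap does not by itself make Part C unacceptable.

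**What to change.** In Appendix 5, Table 3, add a predose Day 4 chemistry and haematology sample for the two sentinel patients. In the Part C synopsis and Sections 3.1.3, 3.4.1 and 5.3, state that release of the remaining six requires the Investigator to review both sentinels' data through the Day 4 visit, including those laboratory results. The decision can stay one of Investigator judgement; no new threshold is needed.

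The cost is one extra tube in each of two patients, at a visit that already draws PK and biomarker blood, and the wait for laboratory turnaround. No visits or patients are added.

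The alternative is to hold release until the existing predose Day 8 result has been reviewed. That gives laboratory data after 7 doses instead of 3 and needs no new sample, but it delays release by about 4 days plus turnaround. Under either option only one sentinel is on active drug, so detection stays limited.
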